**Fig. 1 Fig1:**
[figure not shown]
Participant flow through the trial

Participants eligible to take part in the study will be given or emailed the Participant Information Statement, consent form and safety agreement by the site coordinator. Participants will also be asked to complete the participant contact form for us to be able to contact the participant at each follow-up point.

All participants will be administered the baseline measures, with those randomised to the intervention group given a mobile tablet device loaded with the app and provided with basic training on how to use it, as well as assistance with setting up their personal identification number. Participants in the wait list control condition will be given the mobile tablet and app 6 months after the intervention group. Active participants will be contacted every 3 weeks until the end of the intervention period, and waitlist participants every 4 weeks, via email or telephone for a wellbeing check. Participants in each group will be provided with information about suicide prevention services and mental health services. This involves direct access to suicide prevention crisis support, and referral to medical providers, if sought or if flagged as at-risk during wellbeing checks. In this instance, an Indigenous psychologist or counsellor will contact the participant and provide triage to local services or engage emergency services where required. Following community consultation it was decided that participant retention be supported through regular contact with the study team, and through a $20 gift card reimbursement for completing each assessment. All participants were free to withdraw from the study at any time.

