A pilot RCT of a prototype of the iBobbly app (version 1) was conducted in the Kimberley region of Western Australia between September 2013 and March 2015, involving 61 Indigenous participants aged 18–35 years. Participants were randomised to receive either the app, which delivered acceptance-based therapy over 6 weeks, or were waitlisted for 6 weeks and then received the app for the following 6 weeks. While the between-group changes in suicidal ideation from pre-intervention to post-intervention were not statistically significant, the pre–post intervention change for the iBobbly arm was statistically significant, showing a mean decline of 0.84 (95% CI 0.14–1.53) on the Depressive Symptom Inventory—Suicidality subscale [22]. This corresponds to a moderate effect size of 0.39 (Cohen’s d) and, in a preventive context, justifies further research using the app. In addition, participants in the iBobbly group showed substantial and statistically significant reductions in psychological distress compared with those in the waitlist. Change in impulsivity as measured in the trial was nonsignificant and negligible in size [23].

The current study differs from the pilot study in several ways. The major changes from the pilot study are the inclusion of several additional hypotheses (outlined below) and the inclusion of a cost-effectiveness analysis. This has resulted in additional outcome measures, including more comprehensive measures of suicidality, help-seeking, distress tolerance, interpersonal needs, service use, and quality of life. iBobbly itself is now a substantially different intervention, with major revisions based on feedback from the first pilot and from national consultations with a range of Aboriginal and Torres Strait Islander groups and communities. The study is recruiting a larger sample size from an additional five regions, representing a broader cross-section of Aboriginal and Torres Strait Islander communities. The lower age limit for participants has been reduced from 18 to 16. Finally, longer between-group (6 months) and intervention within-group (12 months) follow-up periods are included.

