## Methods/design

A two-arm randomised controlled trial (RCT) will be conducted (one active intervention/one 6-month wait list control) using three measurement occasions: baseline, post-intervention (after completing the program at week 6), and follow-up at 6 months after baseline assessment. After community consultation, the waitlist control condition was selected as the only acceptable one to the Aboriginal and Torres Strait Islander communities involved in the trial. A SPIRIT checklist (Additional file 1) was completed to address all necessary items in the trial protocol.

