### Community consultation

Following consultation with Aboriginal community members during research design it was decided that to ensure ethical standards and maintain appropriate duty of care, all participants would be provided with information about crisis services and offered referral to clinical services if needed. As such the study examines the impact of iBobbly compared to usual care in the waitlist group. The age range for recruitment was initially 16–35 years; however, following commencement of recruitment, feedback from research sites indicated that many community members over the age of 35 wished to take part and would likely benefit from the app; so to maintain positive relationships with community the upper age limit was removed. The initial follow-up period was to be 24 months but given difficulty with recruitment and feedback regarding burden of numerous follow-up questionnaires the 24-month follow-up was removed with the 12-month remaining as the final follow-up point for the iBobbly group.

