#### Data monitoring and governance

A Data Safety Monitoring Board (DSMB) has been established in accordance with the Australian National Health and Medical Research Council Guidelines. The DSMB is independent of the funders, has no competing interests, and its members are not study investigators. The DSMB is comprised of three senior academics experienced in conducting randomised controlled trials in suicide prevention and mental health. One member is also a biostatistician. The DSMB will receive 6-month data reports and will be notified of adverse events, as required by the human research ethics committee (HREC). Their findings on adverse events will be reported to the HREC. The DSMB has the authority to stop the trial if interim analyses indicate that sufficient sample size has been achieved, or there is sufficient evidence that the intervention is causing harm. Site coordinators will report adverse events to the trial manager within 72 h of notification of the event. Police and postvention services in each site have been asked to advise the trial manager of any deaths by suicide within the region. The investigator team acts as the steering committee. The trial manager reports to the principal investigator, and the principal investigator is responsible for liaising with the DSMB and the HREC. Site coordinators report to the trial manager. Protocol amendments will be reported to the investigators and submitted to all ethics committees for their approval prior to implementation.

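### Wellbeing checks differ by arm and stop at week 6 for iBobbly, so later non-fatal events and check-triggered referrals may be recorded less often in that arm

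*Protocol article*

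**What the plan says.** All references are to the protocol article.

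- **Contact schedule (Procedure, text after Fig. 1).** "Active participants will be contacted every 3 weeks until the end of the intervention period, and waitlist participants every 4 weeks". The contact is a wellbeing check by email or telephone.
- **End of the intervention (Methods/design).** The second measurement is "post-intervention (after completing the program at week 6", so the iBobbly checks end at week 6.
- **Length of the wait.** The design is "one active intervention/one 6-month wait list control", and the Procedure adds: "Participants in the wait list control condition will be given the mobile tablet and app 6 months after the intervention group". No end date is given for the wait-list checks.
- **Compared period (Background).** The article says that "longer between-group (6 months) and intervention within-group (12 months) follow-up periods are included".
- **What a check can trigger (Procedure).** Participants have crisis support and "referral to medical providers, if sought or if flagged as at-risk during wellbeing checks". A psychologist or counsellor then triages to local services or involves emergency services.
- **Harm reporting (Data monitoring and governance).** Site coordinators report adverse events within 72 h of being notified of them. The DSMB may stop the trial if sufficient sample size has been achieved, "or there is sufficient evidence that the intervention is causing harm". Police and postvention services have been asked to report suicide deaths in the region.
- **Description of the control (Community consultation).** "the study examines the impact of iBobbly compared to usual care in the waitlist group".

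**The concern.** A participant can reach referral in two stated ways: by asking for help or by being flagged at a check. The Abstract and Background describe help-seeking in this population as low, so the check matters most for those who do not ask. After week 6 the article schedules checks in the wait-list arm only.

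Two comparisons are exposed:

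- **Harm.** A site must learn of a non-fatal event before it can report it. With fewer scheduled contacts after week 6, such events are liable to be under-recorded in the iBobbly arm. That error is in the falsely reassuring direction, and the DSMB's authority to stop for harm invites a comparison with control.
- **Service use at 6 months.** Checks can themselves generate referrals. Extra wait-list checks could raise control-arm service use. That would flatter the hypothesis of lower crisis-service use with iBobbly, and it would mask the increase in healthcare utilisation named in the secondary aims.

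The control is also not described as delivered: it includes scheduled checks with triage on top of usual care.

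**Working it through.** The article gives no figure for the number of checks, so there is none to reproduce. The sample size calculation plays no part here.

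**Inputs.** iBobbly interval 3 weeks, ending at week 6; wait-list interval 4 weeks, end not stated; compared period 6 months, taken as 26 weeks. Counting the wait-list checks to week 26 is an assumption.

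**Count of scheduled checks per participant.**
- iBobbly: 6 / 3 = 2, at weeks 3 and 6.
- Wait-list: 26 / 4 = 6.5, so 6 checks, at weeks 4, 8, 12, 16, 20 and 24.

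| Period | iBobbly | Wait-list |
|---|---|---|
| Before week 6 | 1 | 1 |
| Up to and including week 6 | 2 | 1 |
| After week 6 to week 26 | 0 | 5 |
| Total over 26 weeks | 2 | 6 |

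Weeks with no check scheduled in the iBobbly arm: 26 − 6 = 20, and 20 / 26 = 77%.

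**Alternative reading.** If the end of the intervention period limits the checks in both arms, the counts are 2 against 1 to week 6 and none in either arm afterwards. The imbalance after week 6 would then disappear. The sentence attaches the limit to active participants, so this is the less natural reading, but the article does not exclude it.

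**How far recording could differ (illustration; detection rates are assumed).** Suppose true non-fatal event rates are equal and spread evenly over 26 weeks. Let q be the chance that a later check picks up an event, and s the chance that any other route does, with the same s in both arms. A later check exists for events in the first 6 weeks with iBobbly and in the first 24 weeks with wait-list.

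- Recorded share, iBobbly: 1 − (1 − s)(1 − q × 6/26)
- Recorded share, wait-list: 1 − (1 − s)(1 − q × 24/26)

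| q | s | iBobbly | Wait-list | Ratio |
|---|---|---|---|---|
| 0.3 | 0 | 0.069 | 0.277 | 0.25 |
| 0.9 | 0 | 0.208 | 0.831 | 0.25 |
| 0.9 | 0.3 | 0.445 | 0.882 | 0.51 |
| 0.6 | 0.6 | 0.655 | 0.822 | 0.80 |
| 0.3 | 0.6 | 0.628 | 0.711 | 0.88 |

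With q from 0.3 to 0.9 and s from 0 to 0.6, a neutral app shows a recorded event ratio of 0.25 to 0.88 instead of 1. The direction is constant. The size depends almost wholly on how good the other routes are, which the article does not say.

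**The case against.** The strongest reply is that bias in harm counts is an inference. The article does not say that adverse events are collected at wellbeing checks, and it describes no between-arm comparison of event counts. This stands: a reader might infer that harm counts are biased, but the text supports only that they are liable to be.

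A reader might also infer that events after week 6 are sought in one arm only, or that the app arm is left unchecked. Neither is supported. Both arms have the 6-month assessment, which may be done face-to-face or by telephone with a site coordinator, and the iBobbly arm has a further one at 12 months. Help can be sought at any time, the Procedure also mentions regular contact with the study team, and suicide deaths have a route that does not depend on arm. How events are solicited may be set out in the full protocol, which is not shown.

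A third tempting reading is that the 6-week primary comparison is distorted by double the contact. The second iBobbly check falls at the 6-week assessment itself, so before it each arm has one check. At 6 months the extra contact is in the wait-list arm; if supportive, it would dilute an app benefit on SIDAS rather than create one. Months 6 to 12 have no comparator and cannot bias a between-arm result.

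Finally, the contact schedule is a matter of participant care agreed with communities, so a statistical review should not prescribe one. This also stands. None of it removes the unequal schedule, which the article states outright and which further detail elsewhere would not make equal.

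**Conclusion.** The point holds in a limited form. Scheduled checks are unequal by stated rule: 2 against 6 over 26 weeks and 0 against 5 after week 6, if the wait-list checks run through the wait. Recording of non-fatal events and check-triggered referrals after week 6 may therefore be lower in the iBobbly arm, which could make the app look safer and could affect 6-month service use.

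The size is unknown; the 0.25 to 0.88 range shows sensitivity to assumptions and is not an estimate. Suicide deaths and the scheduled assessments are not affected in the same way.

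The conclusion assumes that the end of the intervention limits only the iBobbly checks, that sites learn of some non-fatal events through them, and that a 6-month between-arm comparison is made, as the aims, hypotheses and Background state.

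**What to change.** - Reconcile the contact schedule in the Procedure with the 6-month between-arm comparison and with the usual-care description in Community consultation, and state when the wait-list checks end. No particular schedule is proposed; that is for the sponsor and the communities.
- Record the source of each adverse event.
- Base any between-arm harm comparison, for the DSMB and the final report, on sources identical in both arms: the 6-week and 6-month assessments, the Resource Use Questionnaire (RUQ), and police and postvention notices. List events found only at wellbeing checks separately.
- Report the number of checks and of referrals they triggered, by arm. This is also needed to read the RUQ: it is collected alike in both arms, but its content can include referrals that a check set off.
- Describe the control as usual care plus scheduled wellbeing checks.

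The cost is one extra field on the adverse event form, a little more reporting, and fewer events in the main harm comparison. Apart from settling the schedule text, none of this changes participant care.

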### Intervention

iBobbly is a trans-diagnostic app-based self-help program aimed at reducing the frequency and intensity of suicidal ideation. As previously mentioned, the app uses culturally adapted content from ACT, MBCT, and DBT. It consists of three modules that focus on 1) dealing with unhelpful, distressing thoughts, including suicidal thoughts, 2) regulating intense emotions, and 3) values-based goal setting and action planning.

### Assessments

Figure 2 presents the scales that will be administered at the various measurement occasions in the trial. It is estimated that it will take participants 20–30 min to complete each baseline, 6-week, 6-month, and 12-month questionnaires ranged depending on fluency with English. Where possible, scales adapted for or widely used among Aboriginal and Torres Strait Islander people were chosen. Study questionnaires are available by contacting the lead author. Where paper and pen questionnaires are used, data entry is completed either by site coordinators in each region via a secure online portal, or centrally at the Black Dog Institute. Random checks of 25% of questionnaires will be completed to validate the accuracy of data entry against paper questionnaires. Data cleaning will be completed at the end of the data collection period. Participant data are password protected and stored on secure University of New South Wales servers in de-identified form. Paper forms are kept in locked filing cabinets, with electronic transfer occurring via secure web services. All documents will be stored for 5 years after date of publication.

**Fig. 2 Fig2:**
[figure not shown]
Phases of the trial and data collection points

#### Demographic variables

The following demographic variables will be ascertained: age, gender, Aboriginal or Torres Strait Islander status, usual form of accommodation (own residence, parent, boarding, shelter, no fixed address/homeless, other), employment status (full-time, part-time, part-time and looking for full-time work, unemployed/looking for work, not in labour force), usual occupation (free text), educational attainment (some primary, all primary, some secondary, 4 years secondary, 6 years secondary), post-secondary or tertiary schooling (none, trade/apprenticeship, other certificate, diploma, bachelor or higher degree), and relationship status (single, de facto, separated, married, divorced, widowed).

#### Suicidality

The Suicidal Ideation Attributes Scale (SIDAS) [24] is a brief measure of severity of suicidal ideation. The five-item scale assesses frequency (item 1), controllability (item 2), closeness to attempt (item 3), distress (item 4), and interference with daily activities (item 5) over the past month. Respondents answer on an 11-point scale (ranging from 0 to 10) with total scores ranging from 0 to 50. Higher scores indicate greater suicidal ideation. Item 2 (controllability) is reverse scored. Those who endorse a frequency of 0 for the first question skip the remaining items and are given a score of 10 (full control) for item 2 (controllability). The SIDAS is suitable for online use. The scale has demonstrated high internal consistency with Cronbach’s alpha of 0.91, and good convergent validity. In an online survey of community-based Australian adults (*n* = 1352) [24], a cut-off of 1 had sensitivity of 85.5% for suicide plans and 84.0% for suicide attempts (with 67.1% and 63.6% specificity, respectively). However, high specificity is needed to identify individuals most likely to engage in suicidal behaviour. At a cut-off score of 21, the SIDAS has 95.8% specificity for presence of plan in the past year and 94.9% specificity for presence of preparation for or making a suicide attempt in the past year. The suicidal intent and suicidal plan questions of the Quick Inventory of Depressive Symptomatology (QIDS) will be used to assess suicide plans.

#### Help-seeking

The General Help-Seeking Questionnaire (GHSQ) is a brief measure of a person’s intentions to seek help for emotional or personal problems and suicidal thoughts [25]. The measure consists of two questions, the first asking the likelihood of seeking help for an emotional or personal problem and the second asking the likelihood of seeking help for suicidal thoughts. The two questions list 11 possible sources someone might ask for help, e.g. their friend, doctor, etc., and includes the statement “I would not seek help from anyone” as a source. Each source is rated on a seven-point scale from 1 (extremely unlikely) to 7 (extremely likely). The scale demonstrates good reliability (α = 0.83 for the suicidal ideation question and α = 0.70 for the emotional/personal problems question) and validity amongst a sample of Australian high school students [25].

The Resource Use Questionnaire (RUQ) is a modified version of the Client Socio-Demographic and Service Receipt Inventory—European Version (CSRI) [26]. The language in the questionnaire has been simplified to suit Indigenous Australians where English may not be their first language. The RUQ captures service use measures, including contact with mental and primary health care staff and medication usage. A comparison of GP records with data from the CSRI found no significant difference in the average number of GP visits recorded on GP case records (mean = 3.03; sd = 3.49) and on the RUQ (mean = 2.99; sd = 3.67), and the agreement between the two sources was high (concordance correlation coefficient 0.756) [27]. The measure was reviewed by Indigenous staff for appropriateness for economic evaluation within the Aboriginal community.

#### Depression symptoms

The Patient Health Questionnaire (PHQ-9) is the depression scale of the PHQ, and consists of nine items, each scored 0 (not at all) to 3 (nearly every day). Participants are asked to rate how problematic the items have been for them over the past 2 weeks, yielding an overall score ranging from 0 to 27. The scores are grouped into five categories: 0–4 representing no/minimal depression; 5–9 representing mild depression, 10–14 moderate, 15–19 moderately severe, and 20–27 severe depression. The PHQ-9 has demonstrated good internal validity in participants attending primary care clinics (α = 0.89, *n* = 6000) and obstetric patients (α = 0.86, *n* = 3000). It has an acceptable test–retest reliability of kappa = 0.84 [27]. An adaptation of PHQ-9 for Indigenous Australian communities was utilised in this study [28], and a validation study is currently underway [29].

#### Distress tolerance

The 15 items on the Distress Tolerance Scale (DTS) measure a person’s ability to experience and tolerate negative psychological states [30]. Scored on a five-point scale from strongly agree (1) to strongly disagree (5), a higher overall score on the scale indicates a higher perceived capacity to tolerance distress (range = 15 to 75). The DTS has been found to be a valid measure of distress tolerance in a non-clinical university student sample [30] and a wider community sample of smokers [31]. Cronbach’s alpha for the overall scale was found to be 0.91 [31].

#### Interpersonal needs

The Interpersonal Needs Questionnaire (INQ) is comprised of 25 items that measure thwarted belongingness and perceived burdensomeness [32]. The respondent reports how they have been feeling recently on ten items that measure belongingness and 15 items that measure burdensomeness. The items are rated on a seven-point scale from 1 (not true at all) to 7 (very true). Higher overall scores indicate higher levels of thwarted belongingness and perceived burdensomeness (range = 18 to 126). The INQ has been found to be a reliable and valid measure of belongingness and burdensomeness in younger and older adults in clinical and non-clinical samples [32]. Comparable internal consistency coefficients were found for the belongingness (α = 0.85) and the perceived burdensomeness items (α = 0.89) and construct validity data were encouraging (e.g., thwarted belongingness, more so than perceived burdensomeness, correlates with a theoretically related interpersonal construct, i.e., loneliness) [32].

